### Procedure

In order to implement the intervention, a free WhatsApp messaging program under the title of Sunshine and Skin Health will be developed. In this program, the researcher will introduce the study and the researchers; the purpose of the study and the rules of participation in the study will be explained to the participants. Also, the execution process of the plan will be explained in detail. They will receive an invitation to participate in the intervention. Completing the questionnaires immediately after the intervention(T2) and 3-month follow-up (T3) will be done in this program.

### Interventions

#### Sunshine and Skin Health app

Considering the comprehensive access of students to mobile phones and also the interest of adolescence in their appearance, we decided to design an app that allows the user to take a selfie and identify skin color, eye color, gender, and age based on the photo. In the next step, the user must answer seven behavioral questions [32] on a 5-point Likert scale ranging from 1 “never” to 5 “always” as described below:How often did you use sunscreen last month?When the intense sun, you are engaged in outdoor activities (fun, games, shopping, etc.), how often do you get in the shade?How often do you wear a wide-brimmed sun hat when exposed to exposure sunlight during peak hours (10 am to 4 pm)?How often do you wear long-sleeved clothing when exposed to the harsh sun?How often do you wear sunglasses when exposed to sunlight during peak hours (10 am to 4 pm)?How often do you use sunscreen when exposed to sunlight during peak hours (10 am to 4 pm)?Do you use sunscreen again after washing your hands and face?

In the end, the student will see his changed face in the three stages of adolescence, middle age, and old age. Then, educational messages and recommendations about skin cancer risk and prevention methods will be displayed based on the user’s score (Figs. 3, 4, and 5).

**Fig. 3 Fig3:**
[figure not shown]
Graphics of program implementation in the adolescence phase

**Fig. 4 Fig4:**
[figure not shown]
Graphics of program implementation in the middle age phase

**Fig. 5 Fig5:**
[figure not shown]
Graphics of program implementation in the aging phase

The app also has the following capabilities:It can be run on all platforms.This app also offers messages and educational recommendations appropriate to each person’s skin color and eye color.In addition to the app itself detecting skin color, eye color, gender, and age, the user can also enter data manually.

#### WhatsApp app

A 1-week cooperation invitation message is displayed at the end of working with the Sunshine and Skin Health app. The intervention includes 27 health messages based on PMT theory, eight educational files, and a skin cancer clip sent through the WhatsApp app during a week (10 am to 4 pm). At the end of each day, a question related to the health messages, educational file, or clip is proposed, and the participant sends his answer in audio or text. Messages are based on the scientific literature on topics related to improving sun protection behavior [7, 12, 33]. The educational content will be prepared after an extensive literature review on sun protection interventions [33–39]. The educational content will include using sunscreen, looking for shadows, wearing a brimmed hat and sunglasses, and wearing long-sleeved clothes. A video clip will be made with the content on skin importance, symptoms, diagnosis and treatment of skin cancer, change of moles, and ways to prevent skin.

### Strategies to improve adherence to interventions

The app has an attractive design and is easy to use, which helps improve adherence to interventions.

### Relevant concomitant care permitted or prohibited during the trial

There will be no restrictions on concomitant care, which will be monitored carefully during the trial through the questionnaire.

### Outcomes

Data collection from demographic information to measuring sun protection behavior, and PMT constructs including perceived vulnerability, perceived severity, response effectiveness, self-efficacy, reward, perceived response cost, fear, and protective motivation in students will be done with an online self-administered questionnaire. Figure 6 provides a SPIRIT depiction of the schedule of enrollment, interventions, and assessments**.**

**Fig. 6 Fig6:**
[figure not shown]
Study design schedule following the Standard Protocol Items Recommended for Clinical Trials (SPIRIT) guidelines

#### Primary outcome

The primary outcome of this study is the resultant changes between the two groups (intervention and control) immediately after the intervention (T2) in parameters including sun protection behavior and PMT constructs including perceived vulnerability, perceived severity, response effectiveness, self-efficacy, reward, perceived response cost, fear, and protective motivation.

#### Secondary outcomes

The secondary outcome of this study is the resultant changes between the two groups (intervention and control) at the 3-month follow-up (T3) in parameters including sun protection behavior and PMT constructs including perceived vulnerability, perceived severity, response effectiveness, self-efficacy, reward, perceived response cost, fear, and protective motivation.

### Questionnaires

Data will be collected through a self-administered questionnaire at three points: (T1) pre-randomized baseline, (T2) immediately after the intervention, and (T3) 3-month follow-up. All participants will complete a questionnaire that includes socio-demographic characteristics, sunscreen behavior, and PMT constructs.

Socio-demographic characteristics include age, gender, educational level, and parents’ jobs.

Sun protection behaviors will be measured through 7 questions: three questions about using sunscreen and four questions about other protective behaviors, including wide-brimmed sun hat, sunglasses, clothing, and shade-seeking.

The PMT constructs include susceptibility, severity, response efficacy, self-efficacy, reward, perceived response cost, fear, and protection motivation.

### Sample size

The sample size is calculated to detect a minimum relative difference of 20% between both groups at post-assessment. This effect was based on the previous studies’ primary outcome and mean protection motivation scores. Based on the relevant literature [30], with alpha error at 0.05 and statistical power at 0.80, and protection motivation before mean ± SD (5.39 ± 2.17) and after mean ± SD (7.01 ± 1.75), ∆ = 2, *ρ* = 0.05, and *n* = 20 was estimated as 160 people. Therefore the total sample size is 320.

### Data storage and management

All documentation, including informed consent and enrollment information booklets, will be stored with the principal investigator. No personal information will be recorded in the researcher’s WhatsApp contact, and to maintain confidentiality, all student personal information will be removed and replaced with a password-protected RID. After the end of the study period, the data will be stored on a protected computer. They are stored with a password. Only people who are part of the research team will have access to the data. The Steering Committee will hold online meetings every 6 months.

### Data analysis

Descriptive statistics will be used for socio-demographic characteristics including age, gender, educational level, and parents’ jobs. Data will be analyzed with linear mixed models taking into account the repeated measures design of the study. All assessment points will be included in the analyses. The main effect of time and group and the interaction between time and group will be assessed. The primary outcome of this study is the resultant changes between the two groups (intervention and control) immediately after the intervention (T2) in parameters including sun protection behavior and PMT constructs. The secondary outcome of this study is the resultant changes between the two groups (intervention and control) at the 3-month follow-up (T3). Estimates of mean between-group changes from T1 to T2 and T2 to T3 will also be provided. For primary outcomes, an alpha level of 0.05 will be applied. Additional analyses including subgroup analyses will be conducted, for example, to compare the effect of the intervention on behavior and the constructs of protection motivation theory in both boys and girls. *T*-test analyses will be used for between-group mean comparisons for normally distributed continuous data. For sensitivity analysis, all demographic variables will be compared between two groups before data analysis, and if there is a variable that has a significant difference between the two groups, it will be explored in analyses. Also for the behavior variable, we think that the participants’ answers to some behavioral questions will be different, so the behavior variable will be divided into several parts. The primary analysis will be based on the intervention intention population and therefore includes data from all participants providing baseline data previously randomly assigned to one of the two study conditions. Multiple imputation methods will be used to estimate missing data. We plan to perform all statistical analyses following intention to intervention model. Questionnaires are available for participants through a link sent in WhatsApp. The questionnaire is designed in a way that every participant must complete all of the questions to be allowed to send the questionnaire back. If an individual does not send the questionnaire back, we will text a recall message 3 times. If we still do not receive the questionnaire, we will call them. Therefore, we do not expect a large proportion of missing values. If there are, we may use multiple imputation methods to estimate missing data. In case of missing value existence, we may also compare the two groups in every evaluation time after intervention (the day after intervention, 3 months after intervention) in addition to using a repeated measures model.

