**Method/design:**

This randomized controlled trial will be conducted on 320 students on 06/04/2022 in Zahedan. We created mobile applications (Sunshine and Skin Health and WhatsApp apps). Sunshine and Skin Health app allows users to see their changed faces in three stages of adolescence, middle age, and old age based on sun protection behavior. The WhatsApp app has 27 health messages based on PMT theory, eight educational files, and a skin cancer clip that will be sent through WhatsApp during a week. Randomization will be performed using a 1:1 (control: intervention) ratio. The primary endpoint is the group difference in sun-protective behaviors and PMT constructs immediately after the intervention. The secondary endpoint is the group difference in sun-protective behaviors and PMT constructs at a 3-month follow-up. The data will be analyzed in SPSS.22, and the significance level will be considered at 0.05.

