### Trial design

This randomized controlled trial (RCT) is an artificial intelligence technology-based education intervention with two-arm superiority parallel randomized controlled trial with a control group. The primary endpoint is the group difference in sun-protective behaviors and PMT constructs immediately after the intervention (T2). The secondary endpoint is the group difference in sun-protective behaviors and PMT constructs at 3-month follow-up (T3). Randomization will be performed using a 1:1 (control: intervention) ratio.

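### Nine unranked primary outcomes share an alpha of 0.05 with no hierarchy, adjustment or success rule, so 0.05 is not the error rate of an any-one-succeeds primary claim

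*Protocol article*

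**What the plan says.** The abstract, Trial design, Primary outcome and Data analysis sections agree with one another: the primary endpoint is the group difference at T2 in behaviour and in the PMT constructs. The Primary outcome section gives the full list: "parameters including sun protection behavior and PMT constructs including perceived vulnerability, perceived severity, response effectiveness, self-efficacy, reward, perceived response cost, fear, and protective motivation". That is one behaviour outcome plus eight constructs, nine in all, with none placed above the others. Data analysis restates the set as differences "immediately after the intervention (T2) in parameters including sun protection behavior and PMT constructs".

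On the error rate, the abstract says "the significance level will be considered at 0.05" and Data analysis says "For primary outcomes, an alpha level of 0.05 will be applied". No order of testing, multiplicity adjustment, global test or all-must-succeed rule is given.

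Data analysis also says of behaviour, "so the behavior variable will be divided into several parts". The number and content of the parts are not given. The Questionnaires section describes the seven behaviour items as "three questions about using sunscreen and four questions about other protective behaviors".

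The Sample size section uses a single outcome, protection motivation, at alpha 0.05 and power 0.80.

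**The concern.** A significance level describes the primary claim only if it is clear what that claim is. With nine primary outcomes and no success rule, a reader of the results cannot tell whether the trial succeeds when one outcome reaches significance, when behaviour does, or only when all nine do. These readings have very different error rates, and nothing in the text stops the choice being made after the results are known.

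The article's own purpose is narrower than its primary endpoint. The Objectives section aims to improve sun-safe and healthy behaviours, and both the abstract's discussion and the main Discussion tie the conclusion to behaviour. Yet a shift in fear or reward alone could be presented as a significant primary result. The sample size rests on protection motivation, so objective, primary endpoint and sample size do not settle on one outcome.

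This is not detail that the article merely leaves to a statistical analysis plan. The article itself fixes nine primary outcomes and the alpha that applies to them.

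**Working it through.** **Inputs from the article**
- Primary outcomes: 1 + 8 = 9 (Primary outcome).
- Alpha for primary outcomes: 0.05 (Data analysis).
- Design: "two-arm superiority parallel randomized controlled trial" (Trial design). Sidedness is not stated; I take two-sided tests.
- Protection motivation 5.39 ± 2.17 before and 7.01 ± 1.75 after, a 20% relative difference, ρ = 0.05, n = 20, and 160, doubled to a total of 320 (Sample size).

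**Inputs assumed**
- Common correlation among the nine test statistics: not given, so shown from 0 to 0.9.
- Design effect: ρ and n read as intraclass correlation and cluster size, giving 1 + (20 − 1) × 0.05 = 1.95.

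**The plan's own figure.** The article states no familywise error. Its nearest figure is 160 per group. I could not reproduce this from the stated inputs: a difference of 7.01 − 5.39 = 1.62 with pooled SD 1.97 at two-sided 0.05 and 80% power needs 24 per arm, or 47 with the design effect. That is a separate matter. Below, 160 per arm is taken as given.

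**Familywise error, if any one success counts.** For independent tests: 1 − (1 − 0.05)^9 = 1 − 0.95^9 = 0.370.

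For nine equicorrelated normal test statistics, each tested two-sided at 0.05 (simulation, 1,000,000 draws):

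| Assumed common correlation | Chance of at least one false success |
|---|---|
| 0 | 37% |
| 0.3 | 33% |
| 0.5 | 27% |
| 0.7 | 20% |
| 0.8 | 17% |
| 0.9 | 12% |

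Even at 0.9 the error is more than twice the stated 0.05.

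**Familywise error, if all nine must succeed.** It cannot exceed 0.05, so there is no inflation. The cost is then in power, and the single-outcome calculation does not address the power to succeed on all nine.

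**What adjustment would cost.** The first Holm step is 0.05/9 = 0.0056 (two-sided critical value 2.773). Bonferroni at that level gives a familywise error of 1 − (1 − 0.05/9)^9 = 4.9% under independence.
- Pooled SD = √[(2.17² + 1.75²)/2] = 1.97.
- Difference = 0.20 × 5.39 = 1.078.
- Effective size per arm = 160/1.95 = 82.05.
- Standard error = 1.97 × √(2/82.05) = 0.308.
- 1.078/0.308 = 3.50.
- Power at 0.05: Φ(3.50 − 1.960) = 94%.
- Power at 0.0056: Φ(3.50 − 2.773) = 77%.

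For a difference of 1.62, the first-step power stays at 99.4%. With no design effect, the standard error is 1.97 × √(2/160) = 0.220, and first-step power for 1.078 is Φ(4.89 − 2.773) = 98%. The loss therefore depends on the design-effect reading. All these power figures are for protection motivation; the article gives no mean or SD for behaviour.

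**The case against.** Four objections deserve weight.

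**The any-one-succeeds rule is not written down.** The article does not say that each outcome is tested separately or that one success is enough. In strict usage, co-primary outcomes must all succeed, and then nothing is inflated. This stands as a limit: the article does not say that a result on fear or reward alone would make the trial positive, only that it could be claimed. But no all-must-succeed rule is written either, and that gap is the defect.

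**The size depends on an unknown correlation.** All nine scores come from one self-administered questionnaire, so high correlation cannot be excluded. A reader might take 27% as a lower bound. It is not one; it belongs to an assumed correlation of 0.5.

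**Splitting the behaviour score need not add primary tests.** A reader might count seven item-level tests plus eight constructs, 15 in all, for which the error would be 36% at correlation 0.5 and 54% under independence. The text does not support that count. The splitting sentence follows the one on sensitivity analysis and comes before the primary analysis is introduced, and several parts need not mean seven items. Nor does the text say that the split depends on the data: it is announced in advance, from an expectation that answers will differ. What remains is that the parts are unspecified and their status is not stated.

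**A statistical analysis plan may hold a multiplicity rule.** It may, and it is not shown, so no claim is made about the whole plan. Such a rule would, however, have to qualify what the article states about its primary outcomes and their alpha.

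**Conclusion.** The point holds as a defect in the stated definition of the primary outcome and its error rate. Nine outcomes are primary, none is ranked, and 0.05 is applied to them without a success rule. If any one success may be claimed, the familywise error is 37% under independence, about 27% at correlation 0.5 and about 12% at 0.9. These figures rest on two-sided tests, a common correlation that the article does not give, and the any-success reading, which is an inference that nothing in the text contradicts.

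The figures are for nine tests only. They contain no contribution from dividing the behaviour score, and none from how school clustering is analysed, which is a separate question. The matter should be settled before outcome data are examined, because a ranking chosen afterwards would not be credible.

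**What to change.** Choose one of two routes and write it into the Primary outcome and Data analysis sections.

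1. **One primary outcome.** Name a single outcome at T2, tested at two-sided 0.05, and make the other eight secondary. The stated objective points to the total of the seven behaviour items. If that is chosen, the Sample size section should say that 320 was derived from protection motivation, and should give the difference and SD assumed for behaviour.
2. **Nine primary outcomes with Holm.** Keep all nine and apply Holm across them, with a first step of 0.05/9 = 0.0056, stating that any outcome significant after adjustment may be claimed.

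Under either route, specify the parts into which the behaviour variable will be divided and state that their results are supportive only.

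**Cost.** No new data are needed, but the change is more than wording. The Protocol amendments section requires authorization by the ethics committee. Under route 1 the constructs can no longer carry the primary claim alone, alpha stays at 0.05, and a behaviour primary needs a sample-size basis that the article does not yet give. Under route 2, first-step power for protection motivation at a difference of 1.078 falls from about 94% to about 77%, below the planned 80%, if the design effect is 1.95.

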### Description of study settings

This study is a randomized controlled trial (RCT) comparing intervention program with a control group in 10- to 12-year-old elementary school students. The project was implemented from April 2022 to July 2022. This period included participant recruitment, baseline data collection, and intervention (see Fig. 2). Randomization will be multi-stage random performed using a 1:1 (control: intervention) ratio. For this purpose, a list of elementary schools will be prepared. Thus, Zahedan city will be divided into five education districts and randomly selected four schools from each district (one girl’s and boy’s school as the intervention group and one girl’s and boy’s school as the control group). A self-administered questionnaire online will be provided to students through school information channels so that those who volunteer may participate in this research.

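### The T1-to-T2 comparison is a change score rather than baseline-adjusted, and the only covariate rule, for a sensitivity analysis, relies on baseline significance tests

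*Protocol article*

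**What the plan says.** The Data analysis section of the protocol article specifies linear mixed models for repeated measures, with every assessment point included. It describes the effects of interest thus: "The main effect of time and group and the interaction between time and group will be assessed". The primary outcome is the between-group difference in change at T2, and estimates of change from T1 to T2 are promised. No covariate is named for this model, and t-tests are also planned for between-group means.

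The only rule about covariates comes in a sentence on sensitivity analysis. The demographic variables are to be compared between the groups, and "if there is a variable that has a significant difference between the two groups, it will be explored in analyses". The same section and Questionnaires list four such variables: age, gender, educational level and parents' jobs. Gender is also the example given for a subgroup analysis.

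On allocation, Description of study settings says: "Thus, Zahedan city will be divided into five education districts and randomly selected four schools from each district". Within each district, one girls' and one boys' school go to each arm. The Randomization section repeats this, but it and the text just before it also describe randomising individual students after consent and baseline assessment.

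**The concern.** Two choices look weak. First, the baseline score is collected on every student before allocation and is likely to predict the later score. Using it only as one more outcome point makes the T1-to-T2 contrast a difference in mean change. That is a valid comparison but usually not the most precise one, so intervals are wider than they need be.

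Second, a significance test at baseline is a poor way to choose adjustment variables, even for a sensitivity analysis. If allocation is random, a significant difference is a chance finding, and it does not show that the variable predicts the outcome. The set of variables examined then depends on which imbalances turn up, and the undertaking to explore them sets no limit on what is done. With nine primary variables (behaviour and eight theory constructs), that leaves considerable freedom after the data are seen.

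**Working it through.** **The plan's own figures.** The article gives no precision for the T1-to-T2 contrast, so there is no figure to reproduce on this point. Sample size quotes ρ = 0.05 and n = 20 without defining them. If ρ is an intraclass correlation and n a cluster size, then 1 + (20 − 1) × 0.05 = 1.95, close to the stated Δ = 2. It is thus probably not the T1-T2 correlation, and r has to be assumed. The stated 160 per arm is not used to derive anything below.

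**Change score against baseline adjustment.** Assume complete data, equal variance σ² at T1 and T2, student-level correlation r, and no clustering. Apart from a common factor for sample size:

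- group-by-time contrast, T1 to T2: 2σ²(1 − r)
- baseline-adjusted contrast at T2: σ²(1 − r²)
- ratio: (1 − r)(1 + r) / [2(1 − r)] = (1 + r)/2

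| Assumed r | Change, 2(1 − r) | Adjusted, 1 − r² | Ratio | Variance saved | Adjusted N matching 320 by change |
|---|---|---|---|---|---|
| 0.3 | 1.40 | 0.91 | 0.65 | 35% | 208 |
| 0.5 | 1.00 | 0.75 | 0.75 | 25% | 240 |
| 0.7 | 0.60 | 0.51 | 0.85 | 15% | 272 |
| 0.8 | 0.40 | 0.36 | 0.90 | 10% | 288 |

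The last column is 320 × ratio. If the plain T2 difference were reported instead (variance 1 on this scale), adjustment would multiply its variance by 1 − r², that is 0.91, 0.75, 0.51 and 0.36. For any r between 0 and 1, adjustment beats both.

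**Chance flags among the baseline tests.** With k independent tests at 0.05, the chance of at least one false flag is 1 − 0.95^k.

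- k = 4, as listed: 1 − 0.8145 = 18.5%
- k = 5, if the parents' jobs are tested separately: 22.6%
- k = 3, if gender is balanced by design and so rarely flagged: 1 − 0.8574 = 14.3%

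Correlation between age and school grade would change these figures somewhat.

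**Effect of clustering on those tests.** This applies only if whole schools are allocated. As an illustration, take an assumed intraclass correlation of 0.05 for the tested variable and 320/20 = 16 students per school. The design effect is 1 + 15 × 0.05 = 1.75. A nominal two-sided 5% test that ignores it uses an effective threshold of 1.96/√1.75 = 1.48, and so rejects about 14% of the time.

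**District and sex.** No between-district or between-sex variance is given, so no gain can be computed. The cost can be. For a school-level comparison of 20 schools in two groups there are 20 − 2 = 18 degrees of freedom. Additive effects of district (4) and sex (1) leave 13. All ten district-by-sex cells leave 20 − 10 − 1 = 9.

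**The case against.** The strongest reply has four parts.

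- **Scope of the rule.** A reader might infer that significance tests choose the covariates of the primary model. The text does not say so: the sentence opens by confining the rule to a sensitivity analysis, and nothing lets the tests alter the primary model. This stands and limits the point. The rule is still the only one given, and it is a poor one for a sensitivity analysis too.
- **Baseline is used.** A reader might infer that the baseline score is ignored. It is in the model as the T1 outcome, the contrast matches the article's definition of the outcome as change, and it is unbiased under randomisation. This stands, so the loss is one of efficiency only, and it shrinks as r rises.
- **District and sex.** A reader might infer that the omission of allocation strata has been shown to cost precision. That is not supported. The article also describes randomising individual students, in which case these are not strata. Gender appears as a tested demographic and a subgroup; only district is absent from the analysis. The sentence on time and group names effects of interest and need not be an exhaustive list of terms, and a fuller list may sit in an analysis plan not shown.
- **Assumed r.** The 15% to 35% saving rests on assumed student-level correlations. If schools are allocated, the correlation of school means matters as well. This qualifies the size of the saving but does not remove the case for adjustment.

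**Conclusion.** The point holds as a matter of efficiency and of discretion in the analysis, not of validity. As written, the T1-to-T2 contrast is a change-score comparison. Baseline adjustment would reduce its variance by 35%, 25% or 15% at r = 0.3, 0.5 or 0.7, assuming complete data and equal variances and ignoring school clustering. The significance trigger in the sensitivity analysis would flag at least one of four independent variables by chance about 18.5% of the time, and more often for variables that cluster by school if schools are allocated and clustering is ignored. Neither conclusion depends on settling the unit of allocation. The advice on district, school sex and a school effect does depend on it, and its benefit cannot be quantified from the article.

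**What to change.** 1. In the primary model, prespecify the baseline score of the same outcome as a covariate, or keep T1 as an outcome and constrain its mean to be equal across groups.
2. Replace the significance-triggered sensitivity analysis with one that uses a prespecified list of covariates chosen for expected prognostic value. Report baseline characteristics descriptively, without tests.
3. Reconcile the school-level and student-level accounts of allocation in Description of study settings and Randomization. If schools are allocated within district and sex, also include district and school sex as fixed effects and add a random school intercept, which Data analysis does not name.

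The change is to wording. The baseline scores and gender are already collected, and district follows from the school lists. The one statistical cost, under school allocation, is the fall in school-level degrees of freedom from 18 to 13 with additive effects or to about 9 with all ten cells, which favours the additive form. The choice should be recorded before outcomes are compared by group.
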